### Data collection and access

Research variables will be collected at baseline, at hospital discharge, and 1, 3 and 6 months after discharge, with the exception of physical fitness at hospital discharge due to medical contraindication. To discern the effect of the intervention during the pre-surgery and hospitalization period, the presence of frailty, ultrasound examination and inspiratory muscle’s function will be recorded at hospital admission prior to surgery (Table 2). Study data will be collected and managed using REDCap electronic data capture tools hosted at HGUGM [89]. Data validation strategies will be applied to avoid problems with manual data entry. All investigators will be giving access to the cleaned data sets according to the role given within the study.

**Table 2 Tab2:**
[figure not shown]
Data collection schedule for ECOOL-Program

*Qx* Colorectal surgery, *HRQoL* Health-Related Quality of Life, *EORTC QLQ* European Organization for the Research and Treatment of Cancer Quality of Life Questionnaires, *SPPB* Short Physical Performance Battery, *FAC* Functional Ambulation Classification Scale, *HADS* Hospital Anxiety and Depression Scale, *PASE* Physical Activity Scale for the Elderly, *MIP* Maximum Inspiratory Pressure, *SFT* Senior Fitness Test

### Sample size and statistical power

A priori sample size is calculated by estimating the difference between groups in the change in the quality scale of life (EORT QLQ-C30) from diagnosis to 3 months after discharge. A systematic review with meta-analysis pooling 25 clinical trials with a total of 547 cancer patients older than 70 years reported a mean ± standard deviation for global health status of 57.4 ± 23 points in the EORT QLQ-C30 scale [90]. If a difference of 10 points on this scale is considered clinically significant [60], using a two-sided sample t-test at the 5% level of significance with a statistical power (1-β) of 80%, we need to analyze a total of 166 patients. Mortality rate for patients over 74 years of age undergoing CRC surgery at the HGUGM is 4% (unpublished data). Assuming a conservative one-year mortality rate of 20% and an additional drop-out rate of 25% of the patients, we will need around 250 patients (125 per group). Considering a standard deviation of 16.3 points in the Barthel index based on data collected during the CGA for CRC patients conducted during the usual clinical practice at the HGUGM, this sample will be suitable for detecting a 10-points difference between groups, which is larger than the minimal clinically important difference for a geriatric population [91].

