### Randomization and blinding

Patients who fulfill the inclusion criteria and accept to participate will be randomly assigned (1:1) to an intervention (IG) or control group (CG) following a computer-generated (Sealed Envelope Ltd. 2021) allocation sequence using a fixed block size of 6. The allocation sequence and resulting patient assignment will be concealed from study members involved in participants’ enrollment and assessment. Patients will be notified about allocation consignment by the study member involved in the intervention delivery, who will advise to participants not to discuss about their treatment assignment with blinded staff. Participants and care providers will be not blinded to the treatment group. By contrast, data collection and analysis will be performed by researchers blinded to the group allocation of the patients.

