### Statistical analysis

Baseline characteristics of included participants will be analyzed after the total sample have completed the first visit. Descriptive data will be stratified by group allocation and sex. Unless otherwise stated, continuous variables will be presented as mean and standard deviation or median and interquartile range, as required. Categorical variables will be presented as absolute and relative frequencies. Groups will be compared at baseline using Student independent t tests or χ^2^ tests for continuous or dichotomous variables, respectively. For primary and secondary outcomes analyses of continuous variables, the changes observed along repeated measurements will be compared within- and between-group using linear mixed model procedures. Group allocation (IG vs. CG) and repeated measurements (i.e., baseline, hospital admission-discharge and 1-month, 3-month and 6-month after surgery) will be included in the model as fixed factors (i.e., independent categorical variables) while random intercepts will be considered for patients to account for within-subject correlation between repeated measurements. Analyses will be adjusted for potential confounders based on variables with significant between-group differences at baseline or previously described factors affecting the corresponding dependent variable. The models will be calculated considering maximum likelihood estimation and the best-fitting covariance structure. The consistency of the between-group differences will be assessed for subgroups defined by age, frailty, presence of delirium, and baseline functional status. In addition, the proportion of patients who loss, maintain or regain HRQoL, functional and physical capacity baseline values at 3 and 6 months after surgery will be compared by using χ^2^. The effect of the intervention on mortality incidence will be analyzed with Kaplan-Meir curves, Log-rank test and Cox regression analysis. Primary analyses will be conducted based on the intention-to-treat principle. Missing data will be addressed with multiple imputation methods while sensitivity analyses will be employed to evaluate the influence of the multiple imputations. The statistical level of significance will be set at α=0.05.

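### The sample size targets a difference in change but uses the SD of a single-time score, so the stated 80% power rests on an unstated correlation of about 0.5

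*Protocol article*

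**What the plan says.** The section Sample size and statistical power names the quantity being sized as the "difference between groups in the change in the quality scale of life (EORT QLQ-C30) from diagnosis to 3 months after discharge". For variability it draws on a meta-analysis of older cancer patients that "reported a mean ± standard deviation for global health status of 57.4 ± 23 points". It takes 10 points as the difference to detect, uses a two-sided t-test at 5% with 80% power, and concludes that "we need to analyze a total of 166 patients". No SD of change and no correlation between baseline and follow-up is given there or elsewhere in the article.

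The section Statistical analysis plans a linear mixed model that compares changes within and between groups. Group is a fixed factor, and "repeated measurements (i.e., baseline, hospital admission-discharge and 1-month, 3-month and 6-month after surgery) will be included in the model" as the other, with a random intercept per patient. Baseline is thus one of the repeated responses. Adjustment is foreseen for variables that differ at baseline or are known to affect the outcome, but the baseline score is not named among them.

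**The concern.** The SD of a change is not the SD of a score. It depends on how strongly the two measurements are correlated within patients, and can be larger or smaller than the single-time SD. The calculation names one quantity and takes its SD from another, so the power claimed for the sized primary outcome does not follow from the inputs shown.

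The planned analysis matters here. A comparison adjusted for the baseline score has a residual SD no larger than the SD at follow-up, so a single-time SD is a safe input if it is right for 3 months. A change-score comparison has no such protection. As described, the model most naturally yields a change-score contrast at 3 months. At stake is whether the trial has the power it claims for its quality-of-life outcome, and whether the analysis makes good use of a baseline score that is collected anyway.

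**Working it through.** **Inputs from the article.** Difference 10 points; SD 23 (reported with mean 57.4); two-sided 5%; power 80%; 1:1 allocation; 166 analysed, so 83 per arm. **Not in the article:** the baseline to 3-month correlation r, taken below as an assumed range, and the SD at 3 months in this trial, taken as 23 unless stated otherwise.

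**1. Reproduce the plan's figure.** Normal approximation, total N = 2 × 2 × (1.960 + 0.842)² × (SD/difference)².

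With SD 23 and difference 10: 4 × 7.849 × 5.29 = 166.1, matching the stated 166. Rounding up within each arm gives 84 per arm, 168 in total. With 83 per arm, power is 80.0% by the normal approximation and 79.5% by the t distribution. So 23 was entered directly as the SD of the quantity compared.

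**2. What that implies.** With equal SD at both times, SD of change = 23 × √(2(1 − r)). This equals 23 only when 2(1 − r) = 1, that is r = 0.5. By the t distribution, the smallest r giving 80% power with 166 analysed is 0.506.

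**3. Power over a range of r** (t-test, 83 per arm, 10 points). The baseline-adjusted SD is 23 × √(1 − r²).

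| r (assumed) | SD of change | Power, change score | SD, baseline-adjusted | Power, baseline-adjusted |
|---|---|---|---|---|
| 0 | 32.5 | 50% | 23.0 | 79.5% |
| 0.2 | 29.1 | 60% | 22.5 | 81% |
| 0.3 | 27.2 | 65% | 21.9 | 83% |
| 0.4 | 25.2 | 72% | 21.1 | 86% |
| 0.5 | 23.0 | 79.5% | 19.9 | 90% |
| 0.6 | 20.6 | 88% | 18.4 | 94% |
| 0.7 | 17.8 | 95% | 16.4 | 97% |

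For a change score, 80% power would need 236 analysed at r = 0.3 and 136 at r = 0.6.

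**4. Which column fits the planned model.** With complete data and a separate baseline mean for each arm, the group contrast from baseline to 3 months is the difference in mean change, and its variance is that of the change score. The adjusted column would apply if the baseline score were a covariate or both arms shared one baseline mean. The article specifies neither.

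**5. Sensitivity to the equal-SD assumption.** Let the baseline SD be 23 and the 3-month SD be s. The change SD equals 23 when 23² + s² − 2r × 23 × s = 23², which gives r = s/46. The break-even correlation is 20/46 = 0.43 for an assumed s of 20 and 26/46 = 0.57 for an assumed s of 26. The adjusted SD is s × √(1 − r²). With s = 26 it is 25.5 at r = 0.2 and 24.8 at r = 0.3, with power 71% and 73%.

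**The case against.** The strongest reply is that nothing is miscalculated: 10 points and SD 23 do give 166. That is right. The fault lies in the match between the SD and the quantity named, not in the arithmetic.

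A second reply is that the direction is unknown. This also stands. A reader might infer that the trial is underpowered, because major surgery and cancer treatment fall between the two measurements and could weaken the correlation. The article does not support that inference. It gives no correlation, a shift in the mean does not by itself lower the correlation, and above r = 0.5 the plan is conservative.

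Third, the threshold of 0.5 depends on equal SDs at both times, and step 5 shows it moving from 0.43 to 0.57 under modest departures. For the same reason, a reader might take 23 to be a guaranteed upper bound once baseline is adjusted for. It is one only if the 3-month SD in this trial is no more than 23, and the article's figure comes from pooled literature.

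Fourth, the exact form of the mixed model can be left to an analysis plan that is not shown, and the general adjustment sentence does not exclude the baseline score. That is fair as to the model, so the article cannot be said to rule out baseline adjustment. It does not remove the point: the sample-size calculation is set out in full, its SD does not belong to the change it names, and comparing changes with baseline among the responses most naturally reads as a change contrast.

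**Conclusion.** The concern holds as an unsupported power statement. The calculation uses the SD of a score as the SD of a change and so relies on an unstated baseline to 3-month correlation of about 0.5, given equal SDs at the two times. With 166 analysed, change-score power runs from about 60% at r = 0.2 to 95% at r = 0.7. The stated 80% may be too high or too low, and the article gives no means of telling which.

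Adjusting for the baseline score gives more power than the change score at every correlation computed (0 to 0.7) and largely removes the dependence on r, subject to the 3-month SD being no more than 23. All these figures assume that 166 patients are in fact analysed. The point should be corrected, but it does not show that the trial is too small.

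**What to change.** In Statistical analysis, define the primary quality-of-life contrast as the baseline-adjusted difference between groups at 3 months. Either enter the baseline score as a covariate with the post-baseline visits as responses, or keep baseline among the responses and give both arms a common baseline mean.

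In Sample size and statistical power, restate the calculation on that contrast: with a 3-month SD of 23, 166 analysed gives about 80% power or more at any correlation (81%, 83%, 86% and 90% at r = 0.2, 0.3, 0.4 and 0.5). Say that this rests on the 3-month SD being no more than 23.

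If the change score is kept, which is also acceptable, state the assumed SD of change or correlation and show power on both sides of r = 0.5.

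The cost is wording in two sections, with no extra patients or visits, because the baseline score is already collected. The first option does settle the definition of the primary contrast, so it should be recorded as a change to the analysis and made before anyone sees outcomes by group.

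### The sample size is framed on change in QLQ-C30 but uses the SD of a single-time score, so 166 patients give about 80% power only if the diagnosis-to-3-month correlation is about 0.5 or more

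*Protocol article*

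**What the plan says.** Under *Sample size and statistical power*, the protocol article says that the calculation rests on "estimating the difference between groups in the change in the quality scale of life (EORT QLQ-C30) from diagnosis to 3 months after discharge". For the variability it cites a meta-analysis of cancer patients older than 70, which "reported a mean ± standard deviation for global health status of 57.4 ± 23 points in the EORT QLQ-C30 scale". The target difference is 10 points ("If a difference of 10 points on this scale is considered clinically significant"). The test is described as "using a two-sided sample t-test at the 5% level of significance with a statistical power (1-β) of 80" per cent, and the conclusion is that "we need to analyze a total of 166 patients". Allocation is 1:1, so this means 83 per arm.

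The section gives no SD of change and no correlation between the diagnosis and follow-up scores. It does not say that adjustment for the baseline score is the reason for using 23.

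Under *Statistical analysis*, "the changes observed along repeated measurements will be compared within- and between-group using linear mixed model procedures". Baseline is listed there as one of the repeated measurements. Covariates are to be chosen from variables that differ significantly between arms at baseline, or from factors already known to affect the outcome in question. The baseline value of the outcome is not named among them.

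**The concern.** The quantity being sized and the SD used to size it do not belong together. A mean of 57.4 with an SD of 23 describes how patients' global health scores are spread at one time. A t-test on change needs the spread of the within-patient difference, and that depends on how closely a patient's 3-month score tracks the score at diagnosis. The two SDs agree at only one value of the correlation.

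This is the plan's only full power calculation, and it concerns a primary outcome. Anyone reading the eventual quality-of-life result, especially a null one, will take the 80% at face value. Surgery falls between the two assessments and adjuvant treatment may, so a modest correlation cannot be ruled out. Nor can a high one. The point does not depend on how losses are allowed for: it holds even if all 166 patients are analysed.

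**Working it through.** **Inputs from the article.** Difference 10 points; SD 23; two-sided 5%; power 80%; 1:1 allocation; 166 to be analysed (83 per arm).

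**Inputs assumed here.** Correlation ρ between the diagnosis and 3-month scores, taken from 0.2 to 0.8 because the article gives none; equal SD (23) at both times.

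**Step 1: reproduce 166.** The normal approximation gives n per arm = 2 × (1.960 + 0.842)² × 23² / 10² = 83.04. Rounded down this is 83, or 166 in total. Rounded up it is 84, or 168. The t-test calculation gives 84.01 per arm, rounded up to 85, or 170. Power at 83 per arm is 80.0% (normal) or 79.5% (t-test). The article's figure is therefore reproduced, and it comes from SD 23 entered as it stands.

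**Step 2: SD of a change.** Var(change) = 23² + 23² − 2ρ × 23², so SD of change = 23 × √(2(1 − ρ)). Setting this equal to 23 gives 2(1 − ρ) = 1, that is ρ = 0.5. Example at ρ = 0.3: 23 × √1.4 = 27.2.

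**Step 3: SD for a baseline-adjusted 3-month score.** Residual SD = 23 × √(1 − ρ²), which cannot exceed 23. Example at ρ = 0.3: 23 × √0.91 = 21.9.

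**Step 4: t-test power for 10 points with 83 per arm.**

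| ρ (assumed) | SD of change | Power at 166, change | Total N for 80%, change | Adjusted SD | Power at 166, adjusted |
|---|---|---|---|---|---|
| 0.2 | 29.1 | 60% | 268 | 22.5 | 81% |
| 0.3 | 27.2 | 65% | 236 | 21.9 | 83% |
| 0.4 | 25.2 | 72% | 202 | 21.1 | 86% |
| 0.5 | 23.0 | 79.5% | 170 | 19.9 | 90% |
| 0.6 | 20.6 | 88% | 136 | 18.4 | 94% |
| 0.7 | 17.8 | 95% | 102 | 16.4 | 97% |
| 0.8 | 14.5 | 99% | 70 | 13.8 | 99.6% |

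**Step 5: does the planned model remove the dependence on ρ?** Not as described. The model treats baseline as one of the repeated outcomes. With complete data and a separate mean for each arm at each visit, its 3-month contrast is the difference in mean change, which carries the change-score variance in the third column's calculation.

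**The case against.** The strongest reply is that 23 is a sound and even cautious choice for a closely related analysis. Under randomisation the expected difference in change equals the expected difference at 3 months. If the 3-month score is compared with adjustment for the diagnosis score, 166 patients give about 80% or more at any ρ. The analysis section also leaves room for such adjustment through its clause on known prognostic factors. This stands as a reason why the problem is cheap to cure. It does not remove the mismatch, because neither section commits to that contrast and the sizing section names a different one.

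It can also be said that a journal article condenses a fuller protocol, where an SD of change may be justified. That is possible, but the objection is to what the article does state: one quantity is named and the SD of another is used.

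A reader might infer two stronger claims, and the article supports neither.

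- *That the trial is underpowered.* No correlation is given. Above 0.5 the power for change exceeds 80%. That ρ may be low because of surgery or adjuvant treatment is a judgement with no figure behind it.
- *That the Barthel statement has the same fault.* That statement speaks of a 10-point difference between groups and is not framed as change. Even read as change with its SD of 16.3, t-test power at 83 per arm is 79% at ρ = 0 (SD 16.3 × √2 = 23.1) and 87% at ρ = 0.2. The claim holds at essentially any non-negative correlation.

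**Conclusion.** The point holds as a mismatch between the SD and the contrast. It is not an arithmetic error, since 166 follows from the inputs used. For the change contrast that the article names, 166 analysed patients give at least about 80% power only if ρ is about 0.5 or more. Over assumed correlations of 0.2 to 0.8 the power runs from 60% to 99%, so the claimed figure could be too high or too low, and the article does not let a reader tell which. These figures assume equal SDs at both times, that 23 applies to this population, and that all 166 are analysed. The point is confined to QLQ-C30. It merits correction because it concerns the formal power statement for a primary outcome and the cure is cheap.

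**What to change.** In *Sample size and statistical power*, do one of the following.

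1. **Preferred.** Define the QLQ-C30 sizing contrast as the 3-month score adjusted for the diagnosis score, and say the same in *Statistical analysis*. State that 23 is then an upper bound on the relevant SD, so that 166 gives about 80% as a floor (81% to 99.6% for ρ from 0.2 to 0.8).
2. **Otherwise.** Keep the change contrast, state and justify the assumed SD of change or ρ, and restate the power for 166 over ρ from 0.2 to 0.8.

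If paired diagnosis and 3-month scores have already accrued, check the assumption with the SD of change and the correlation pooled over arms, without unblinding, and report the updated power.

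The cost is a few lines of text and, where data allow, one arm-blind calculation. The diagnosis score is already collected and no extra patients are needed. Under the second option the stated power may become less favourable.

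### The target of 250 does not leave the required 166 evaluable patients under the plan's own loss allowances: 150 or about 138 remain, with power near 75% or 72%, not 80%

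*Protocol article*

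**What the plan says.** The Protocol article, section Sample size and statistical power, sizes the trial on the between-group difference in change in the EORTC quality-of-life score from diagnosis to 3 months after discharge.

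- Spread, from a cited meta-analysis: "reported a mean ± standard deviation for global health status of 57.4 ± 23 points".
- Target difference: "If a difference of 10 points on this scale is considered clinically significant".
- Result, for a two-sided t-test at the 5% level: "with a statistical power (1-β) of 80%, we need to analyze a total of 166 patients".
- Allowance for losses: "Assuming a conservative one-year mortality rate of 20% and an additional drop-out rate of 25% of the patients, we will need around 250 patients", that is, 125 per group.

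Between the last two statements the section reports a 4% mortality rate from the hospital's own unpublished data, without a time horizon. It does not show how 166 becomes 250, and it does not scale the one-year mortality to a shorter period. The section Randomization and blinding gives 1:1 allocation.

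**The concern.** An allowance for losses should make the number left after those losses at least equal to the number the power calculation needs. Here the required number, the two loss rates and the recruitment target are all printed, so this can be tested directly. Losses of 20% plus a further 25% amount to 40% or 45% of those randomised, but 250 can lose only 1 − 166/250 = 33.6% before it falls below 166.

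This is the only power calculation for health-related quality of life, which is a primary outcome. If it does not hold, a null result on that outcome would be read as coming from a trial with 80% power when the stated assumptions support less. The 10-point threshold is also the one the protocol itself calls clinically relevant, so power at that threshold is what readers will look for.

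**Working it through.** **Inputs** (all from Sample size and statistical power, except allocation): difference 10; SD 23; two-sided α 0.05; power 80%; 1:1 allocation; 166 to analyse; mortality 20% (one-year); additional drop-out 25%; target about 250.

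**1. Reproduce 166.** The normal approximation gives n per arm = 2 × (1.960 + 0.842)² × (23/10)² = 83.04, or 166 in total after rounding to 83 per arm. The exact t-test needs 84 per arm, 168 in total. The stated 166 is therefore sound to within two patients; its t-test power is 79.5%.

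**2. Try to reproduce 250 from 166 with both rates in full.**

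| Calculation | Result |
|---|---|
| 166 × 1.20 × 1.25 (multiply by one plus each loss) | 249.0 |
| 166 × 1.45 (multiply by one plus the sum) | 240.7 |
| 166 / (0.80 × 0.75) (divide, losses in turn) | 276.7 → 277 |
| 166 / (1 − 0.45) (divide, losses added) | 301.8 → 302 |

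Of these, only the first lands on about 250. Mixed forms do not either: 166/0.80 × 1.25 = 259.4 and 166 × 1.20/0.75 = 265.6.

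**3. Apply the stated losses to 250.**

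- In turn: 250 × 0.80 × 0.75 = 150.
- Added: 250 × 0.55 = 137.5, about 138.

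This step does not depend on how 250 was obtained.

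**4. Power and detectable difference** (t-test, difference 10, SD 23, two-sided 5%).

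| Evaluable | Power | Type II error | Difference detectable at 80% power |
|---|---|---|---|
| 166 | 79.5% | 20.5% | about 10.1 |
| 150 | 75.3% | 24.7% | about 10.6 |
| 138 | 71.8% | 28.2% | about 11.1 |

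Against the stated 20%, type II error is larger by a factor of 24.7/20 = 1.23 in the first case and 28.2/20 = 1.41 in the second.

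**5. How much rests on the one-year rate.** Assume a constant hazard (an assumption that is not in the document) and scale the 20% to the visit, keeping drop-out at 25%.

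- 3 months: survival 0.80^0.25 = 0.946; 250 × 0.946 × 0.75 ≈ 177 evaluable; power about 82%.
- 6 months: survival 0.80^0.5 = 0.894; 250 × 0.894 × 0.75 ≈ 168 evaluable; power about 80%. In reverse, 166 / (0.894 × 0.75) = 247.5.

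**6. Barthel statement.** For 10 points with SD 16.3, power is about 96% with 150 evaluable and about 95% with 138. It survives either loss scenario.

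**The case against.** The strongest reply is that the mortality allowance is a one-year figure, is described as conservative, and stands beside an observed 4%. Fewer deaths should be expected by the 3-month endpoint. If the rate is scaled to 6 months at constant hazard, proper division gives 247.5, so 250 could have been reached without any error. This has force. It means the multiplication in step 2 is an inference and cannot be reported as fact, and that actual power may be at or above 80%. It does not rescue the paragraph, which states no scaling and sets the 20% beside the drop-out rate as a full allowance. A reader cannot tell which loss rate supports 250.

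A second reply is that the planned mixed model and multiple imputation may recover information from partly observed patients. They may recover some. But the section sizes a t-test on patients analysed and claims no such credit.

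A third is that the target is only approximate. Rounding does not cover a gap of 27 (277 − 250) to 52 (302 − 250) patients.

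Two stronger readings are tempting. A reader might infer that the design has been shown to be underpowered; the documents do not support that, because the shortfall depends on applying a one-year rate in full at 3 months. A reader might also infer that baseline adjustment restores the power. The section Statistical analysis places baseline among the repeated measurements of a random-intercept model and does not specify an analysis of covariance, and no baseline-to-follow-up correlation is given, so no power figure for such an analysis can be credited.

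**Conclusion.** The point holds as an internal inconsistency. Under the plan's own 20% and 25% losses, 250 randomised leave 150 or about 138 evaluable patients, not 166, and power for 10 points is about 75% or 72%, not 80%. The loss is moderate: about 4 to 8 percentage points against the 79.5% that 166 patients give, with the detectable difference rising to between 10.6 and 11.1 points. This rests on taking both stated rates at face value and on the plan's own t-test framing with SD 23.

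The inflation by one plus each loss is the likely cause but is not shown. The mismatch between a one-year mortality rate and an endpoint 3 months after discharge is a second weakness in the same sentence, and it works the other way: a rate matched to the endpoint could support 250. Type I error, estimation and the Barthel claim are untouched.

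**What to change.** Keep 250 and rewrite the paragraph in one of two ways.

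(a) Retain the 20% and 25% and state what they imply: about 150 evaluable and about 75% power if the losses apply in turn, or about 138 and 72% if they add. Say which is meant.

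(b) Replace the one-year mortality with a justified rate for the 3-month endpoint, give its source and horizon, and recompute by dividing 166 by the fraction retained. As an illustration only, constant-hazard scaling of the 20% gives about 177 evaluable and 82% power. If the hospital's 4% is preferred, its time horizon must be stated first; taken as the rate by the endpoint, it would give 250 × 0.96 × 0.75 = 180 evaluable and about 83% power.

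Under either option, print the inflation formula. Do not add a power figure for a baseline-adjusted analysis that the plan does not specify. The Barthel sentence needs no change on this account.

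The cost is one reworded paragraph and no extra patients. Under (a) the stated power is less favourable than now; under (b) the sponsor has to justify a mortality rate.
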